Stages A and B will serve to re-confirm the U.S. data on the safety of these products, which will be done in two steps - first in 10 subjects (Stage A) and then in 90 subjects (Stage B). Having found an optimal safe dose for each antigen, both reagents will then be tested in 80 leprosy patients, 40 contacts of leprosy patients, and 40 tuberculosis patients (Stage C), and the results compared with the licensed TB reagent tuberculin/PPD. If the study results indicate that one or both leprosy skin test antigens show specificity and sensitivity in the order of 90% or above, future studies will be planned to measure the extent of leprosy infection in communities around the world, particularly the high prevalence countries of India, Nepal, Brazil, and some of the African countries.

Study Hypothesis: Both leprosy skin test antigens, MLSA-LAM and MLCwA at doses of 1.0µg and/or 0.1µg, will be safe and efficacious as diagnostic-epidemiological tools to detect and treat patients earlier and to measure the extent of leprosy infection in human subjects living in a leprosy endemic area.

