### 13.6.2 Leprosy Detection/Diagnosis

The utility of a medical diagnostic test is often expressed in terms of the receiver operating characteristic (ROC) for the test (37). The ROC is a plot of the relationship between the false positive rate (FPR), or 1-specificity, and the true positive rate (TPR), or sensitivity. Given a pair of individuals, one with and one without the medical condition of interest, the area under the ROC curve (AUC) is equal to the probability that the test will correctly discriminate between this pair. This study will be the first one using these test antigens in volunteers with the condition of interest making it difficult to establish a hypothesis concerning the AUC.

The study design provides for a variety of possible subset analyses for a given dose of each antigen. Nine combinations of volunteers expected to be non-reactive and reactive respectively are listed in the following table. This is not a definitive Phase III trial, although it has some characteristics in that specificity/sensitivity are considered in the analysis, thus adjustments for multiple comparisons are not considered here. The multiple comparison possibility will be considered at the time of actual data analysis.

Although the observational unit in this study is an individual injection site, the experimental unit is subject. Since subjects in C-1 will receive the higher dose of antigen and C-1b subjects the lower dose, results from C-1 and C-1b will not be combined to construct the ROC curve or to estimate the sensitivity/specificity of the antigens. However, independently, C-1 or C-1b will be used construct the ROC curve and estimate the sensitivity and specificity for each dose of the antigen separately. The estimates and sample sizes in the remainder of this section reflect this.

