ROC analyses involve both the expected positive and negative responding groups. Sensitivity and specificity analyses are restricted to each of these groups individually. The following table provides an indication of the precision obtainable in measuring sensitivity and specificity in this study, as determined by the half width of the confidence interval for some hypothetical results and appropriate sample sizes, as described above. Precision decreases as the observed proportion approaches 0.5 and as the sample size is decreased. Therefore, the worse case scenarios for sensitivity analyses would be restricting to BT/TT patients ( $N=36$ ) and observing a 50% sensitivity. In that case, the precision would be 0.16 or a confidence interval of (0.34, 0.66). At the other extreme, if all contacts of BL/LL plus BT/TT ( $N=72$ ) patients are included in the

analyses and a 0.95 sensitivity is observed, the precision is 0.05, or a confidence interval of (0.90, 1.00).

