**Precision of Observed Sensitivity**

| Sample Size | Observed Sensitivity/
Specificity | Precision based on Half-Width of 95% CI |
|-------------|--------------------------------------|-----------------------------------------|
| 36          | 0.5                                  | 0.16                                    |
|             | 0.75                                 | 0.14                                    |
|             | 0.9                                  | 0.10                                    |
|             | 0.95                                 | 0.07                                    |
| 72          | 0.5                                  | 0.12                                    |
|             | 0.75                                 | 0.10                                    |
|             | 0.9                                  | 0.07                                    |
|             | 0.95                                 | 0.05                                    |

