### 13.9.3 Diagnostic Sensitivity/Specificity

These analyses will involve the selection of a cut-off for diagnostic testing, using the test antigens by dose, construction and comparison of ROC curves, and the determination of the sensitivity and specificity of the test antigens based on the selected cutoff points. This work will be based on the induration stimulated by the test antigens.

The text *Statistical Methods in Diagnostic Medicine* (37), will serve as a reference for most of the methods used in these analyses. An important assumption for many of these methods is that the distribution of the outcome measure (induration) follows an approximate binormal distribution, i.e. a combination of two normal distributions, one for the population with the condition of interest and another for the population without the condition. This assumption will be examined and exploited if it is met. Assuming that there is not a complete or virtually complete separation between the groups in their response, methods described by Schaefer, et.al. (38) will be examined to construct a cut-off for each of the antigens at each dose. For each cutoff the 95% confidence interval for the sensitivity and specificity based on this cutoff will be constructed. ROC curves will be constructed, the area under the curve and its 95% confidence interval computed and the antigens/doses will be compared to determine if there is a statistically significant difference in area.

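### The precision figures in 13.6.2 are symmetric Wald half-widths, which near 0.90 and 0.95 do not give 95% intervals; the printed limits (0.90, 1.00) are too favourable

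*Protocol*

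**What the plan says.** Section 13.6.2 of the protocol describes precision "as determined by the half width of the confidence interval for some hypothetical results and appropriate sample sizes". The table column is headed "Precision based on Half-Width of 95% CI" and gives, for observed values of 0.5, 0.75, 0.9 and 0.95:

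- N=36: 0.16, 0.14, 0.10, 0.07
- N=72: 0.12, 0.10, 0.07, 0.05

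The text turns two of these into limits. The worst case is 0.5 at N=36: "In that case, the precision would be 0.16 or a confidence interval of (0.34, 0.66"). The best case is at N=72: "a 0.95 sensitivity is observed, the precision is 0.05, or a confidence interval of (0.90, 1.00").

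The formula is not named. Section 13.9.3 says of the analysis: "For each cutoff the 95% confidence interval for the sensitivity and specificity based on this cutoff will be constructed", again without a method. Section 2.2 links later work to antigens that "show specificity and sensitivity in the order of 90% or above, future studies will be planned". Section 13.6.2 also states that "results from C-1 and C-1b will not be combined to construct the ROC curve or to estimate the sensitivity/specificity of the antigens".

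**The concern.** The worked example shows the symptom. An observed sensitivity of 0.95 in 72 subjects means between three and four failures (72 × 0.05 = 3.6). A true sensitivity of 1.00 is then impossible, yet the printed interval extends to it. A symmetric interval around a proportion close to 1 sits too high: the upper end runs to or past 1, and the lower end is too near the estimate.

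Estimating sensitivity and specificity is a primary objective (section 3.1), and section 13.5 says that no formal hypothesis is tested. Interval precision is therefore a main argument for the diagnostic sample size. A reader who takes the best case at face value would believe that 0.95 observed in 72 subjects places sensitivity at 0.90 or higher with 95% confidence.

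**Working it through.** **Inputs.** Observed values, n=36 and n=72, the 95% level and the half-width measure come from 13.6.2. The 18 evaluable subjects per group and stage (20 less 10%) come from 13.6.1.

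**Step 1: reproduce the table.** Wald half-width = 1.96·√(p(1−p)/n). For 0.95 at n=72: 1.96·√(0.95·0.05/72) = 0.0503, with limits 0.8997 and 1.0003, printed as 0.90 and 1.00. All eight cells match. Wilson, Agresti-Coull and Clopper-Pearson each miss at least one cell; Wilson, for instance, gives 0.080 at 0.95, n=36 (printed 0.07) and 0.1125 at 0.5, n=72 (printed 0.12).

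**Step 2: recompute the limits.** Wilson centre = (p + z²/2n)/(1 + z²/n); half-width = z·√(p(1−p)/n + z²/4n²)/(1 + z²/n). For 0.95, n=72: centre (0.95 + 0.0267)/1.0534 = 0.927, half-width 0.054, limits (0.873, 0.981). Clopper-Pearson uses beta quantiles at x = np.

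| n | Observed | Printed half-width | Wald limits | Wilson limits | Clopper-Pearson limits |
|---|---|---|---|---|---|
| 36 | 0.50 | 0.16 | 0.337, 0.663 | 0.345, 0.655 | 0.329, 0.671 |
| 36 | 0.75 | 0.14 | 0.609, 0.891 | 0.589, 0.862 | 0.578, 0.879 |
| 36 | 0.90 | 0.10 | 0.802, 0.998 | 0.761, 0.962 | 0.754, 0.975 |
| 36 | 0.95 | 0.07 | 0.879, 1.021 | 0.826, 0.987 | 0.821, 0.995 |
| 72 | 0.90 | 0.07 | 0.831, 0.969 | 0.809, 0.950 | 0.806, 0.958 |
| 72 | 0.95 | 0.05 | 0.900, 1.000 | 0.873, 0.981 | 0.871, 0.988 |

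In the 0.90 and 0.95 rows the lower limit falls by 0.02 to 0.05 under Wilson. An exact 0.95 of 72 is 68.4 subjects, so it cannot occur. For 68/72 the intervals are Wald (0.892, 0.997), Wilson (0.866, 0.978) and Clopper-Pearson (0.864, 0.985).

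**Step 3: exact coverage.** Sum the binomial probabilities of every count whose nominal 95% interval contains the true p.

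| | p=0.50 | p=0.75 | p=0.90 | p=0.95 |
|---|---|---|---|---|
| Wald, n=36 | 93.5% | 94.5% | 88.0% | 84.0% |
| Wilson, n=36 | 93.5% | 96.8% | 95.4% | 96.8% |
| Wald, n=72 | 95.6% | 94.3% | 92.7% | 87.8% |
| Wilson, n=72 | 95.6% | 96.0% | 95.4% | 97.3% |

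**Step 4: direction of the misses.** At n=36, p=0.95, the Wald lower limit lies above the truth only when all 36 are positive, where the interval collapses to a point at 1.00. That has probability 0.95³⁶ = 15.8%, against a nominal 2.5%. At n=72, p=0.95, it happens for 71 or 72 positives: 72·0.05·0.95⁷¹ + 0.95⁷² = 11.9%.

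**Step 5: per-dose sizes.** The table's 36 and 72 combine the two dose stages (2 × 18 and 4 × 18), which 13.6.2 rules out. Per dose, one group has 18 and two groups have 36. At n=18, Wald coverage is 84% at p=0.90 and 60% at p=0.95. An 18/18 result, with probability 0.95¹⁸ = 40% at p=0.95, would give a zero-width interval.

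**The case against.** The best counter-argument is that little in the printed column moves. Under Wilson, six of the eight half-widths are unchanged to two decimals, including the quoted 0.05 (0.054) and both 0.90 entries (0.101 and 0.071); one narrows and only one widens. The table is offered as an illustration on hypothetical results, and no sample size or success rule is derived from it. The upper limit of 1.02 at 0.95, n=36 is not printed; it appears only when 0.07 is added to 0.95. The sample-size inconsistency in the same table widens every half-width by about 41% (a factor of √2), more than a change of formula does.

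All of that stands, and it limits the point. It does not remove it, because the fault is in where the interval sits more than in its width. The protocol itself adds and subtracts the half-width to state limits, and near 0.95 those limits are not 95% limits.

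Three stronger readings are tempting and are not supported:

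- **That the final analysis will use Wald intervals.** Section 13.9.3 names no method, and leaving this to an SAP that is not shown is no fault.
- **That the trial has a 90–95% target decided by a confidence limit.** Section 2.2 speaks only of values that "show specificity and sensitivity in the order of 90% or above", as a prompt for future studies, and mentions no limit.
- **That coverage falls to 60% at the printed sizes.** That figure belongs to n=18, which is not in the table.

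**Conclusion.** The point holds for the printed figures in the 0.90 and 0.95 rows and for the best-case example. Coverage there is 84.0% to 92.7% instead of 95%. The printed lower limit of 0.90 is about 0.03 too high, and the upper limit of 1.00 is incompatible with observed failures. The 0.5 and 0.75 rows have coverage of 93.5% to 95.6% and need no correction on this ground; the printed (0.34, 0.66) agrees with Wilson to about 0.01.

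This is a modest but real error in a stated figure. It rests on identifying the formula from the eight printed values, which only Wald fits throughout, and on simple binomial sampling at a fixed cut-off. It is separate from the sample-size question: correcting n alone would leave the formula in use where it performs worse. For 0.95, the lower limit goes from 0.900 (Wald, n=72) to 0.879 (Wald, n=36) and then to 0.826 (Wilson, n=36).

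**What to change.** In 13.6.2, replace the half-width column with lower and upper Wilson (or Clopper-Pearson) limits, name the method, and recompute both worked examples. If the printed sizes were kept, the best case would read (0.87, 0.98) by Wilson or (0.87, 0.99) by Clopper-Pearson.

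Make the change together with correcting n to the per-dose sizes. Wilson limits would then be:

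| n | 0.50 | 0.75 | 0.90 | 0.95 |
|---|---|---|---|---|
| 18 | 0.29, 0.71 | 0.52, 0.89 | 0.69, 0.97 | 0.75, 0.99 |
| 36 | 0.34, 0.66 | 0.59, 0.86 | 0.76, 0.96 | 0.83, 0.99 |

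Use the same interval for the confidence intervals in 13.9.3, so that planning and reporting agree; one sentence is enough.

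The cost is a recomputed table and a few words, with no additional subjects, visits or procedures. The downside is that the stated limits become slightly less favourable from the formula alone, and clearly less so once n is also corrected.

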**Precision of Observed Sensitivity**

| Sample Size | Observed Sensitivity/
Specificity | Precision based on Half-Width of 95% CI |
|-------------|--------------------------------------|-----------------------------------------|
| 36          | 0.5                                  | 0.16                                    |
|             | 0.75                                 | 0.14                                    |
|             | 0.9                                  | 0.10                                    |
|             | 0.95                                 | 0.07                                    |
| 72          | 0.5                                  | 0.12                                    |
|             | 0.75                                 | 0.10                                    |
|             | 0.9                                  | 0.07                                    |
|             | 0.95                                 | 0.05                                    |

### 13.7 Participant Enrollment and Follow-Up

A total of 260 subjects will be recruited for this trial, 10 subjects for Stage A, 90 subjects for Stage B, and 160 subjects for Stage C (80 each in C-1 and C-1b). The total estimated duration of recruitment of subjects to participate in this study is expected to be no less than 1 month and no greater than 1 year for each stage. (Stage A, B, and C-1 was completed prior to the amendment of this protocol.) Completion of Stage C-1b is expected to take approximately 3 months. Total involvement of an individual participant from administration of study product to final follow-up is expected to be no longer than 28 days.

Seven clinical sites have been selected to participate in this clinical study. Stages A and B were performed at one or more of the following Kathmandu campuses in Nepal: Lalitpur Nursing Campus, Sanepa, Kathmandu; The Central Department of Microbiology, Tribhuvan University, Kirtipur, Kathmandu; and The Institute of Medicine, Tribhuvan University, Maharajgunj, Kathmandu. Stages C-1 and C-1b will be performed at some or all of the above mentioned Kathmandu campuses and/or these additional campuses: AH, Patan Hospital TB Clinic, Lalagadh Leprosy Hospital, and Green Pastures Leprosy Hospital. Other campuses/hospitals may also be selected to participate.

### 13.8 Planned Interim Analyses

Interim analyses planned for this study are all directed at monitoring safety and the overall conduct of the trial. These analyses should not impact the Type I error, or equivalently the length of confidence intervals, for the primary computations of sensitivity and specificity at the end of the trial.

Members of the SMC will be composed of an independent group of physicians with relevant experience, including the ISM. The DMID PO and a Biostatistician will serve as non-voting members. The SMC will be convened by the DMID PO at the following time points:

- At the beginning of the study: A chair will be selected and the SMC will discuss procedures for study review.
- After the completion of Stage A: The SMC will submit a report to DMID, NHRC, and the CSU IRB for review and approval before Stage B is initiated.
- After the completion of Stage B: The SMC will submit a report to DMID, NHRC, and the CSU IRB for review and approval before Stage C is initiated.
- After the completion of Stage C-1: The SMC will submit a report to DMID, NHRC, and the CSU IRB.
- After the completion of Stage C-1b (the end of the study): The SMC will submit a report to DMID, NHRC, and the CSU IRB summarizing participant safety.
- In response to AE reporting, any SAEs deemed associated or not associated to the skin test antigens will be reviewed by the ISM and the DMID PO, who may convene the SMC. A report will also be submitted to the SMC for review in the event a number of AEs occur that are apparently associated with a particular antigen.

The primary charge to the advisory members is to monitor safety, study conduct, and study progress, as well as accumulated data. The committee also provides advice to DMID and the study investigators as to the appropriateness of continuing the study as designed. Monitoring bodies are advisory to DMID and their recommendations, while given careful consideration, are not binding.

Statistical interim analysis will be presented in tabular form, including but not limited to: listing demographic characteristics by subject ID and readers' assessments of erythema and measurements of induration; summary of skin test readings by subject ID, antigen code, response after ~15-minutes, ~30 minutes (for stage C1b only) and follow-up examination; and listing of all adverse events (including observations noted approximately at 15-30 minutes). Guidelines for stopping the study have been described in Section 10.2.2., "Criteria for Discontinuation of Study Intervention/Product for Withdrawal of a Subject (or a Cohort)".

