**Stage B: Safety Study in Non-Contacts (Full-Scale)**

| Stage | Group | Sample/Size        | Antigens                              | Dose                            | Intervention*                                                                                                                                             |
|-------|-------|--------------------|---------------------------------------|---------------------------------|-----------------------------------------------------------------------------------------------------------------------------------------------------------|
| B     | 1     | 45
Non-Contacts | MLSA-LAM
MLSA-LAM
PPD
Saline | 1.0 µg
0.1 µg
5 TU
N/A | Day –10 to –1: Recruitment
Day 0: Consent, Physical Exam, Pregnancy Test, History, Administer Antigens (~15 minute)
Day 3 (69-75 h): Reading |
|       | 2     | 45
Non-Contacts | MLCwA
MLCwA
PPD
Saline       | 1.0 µg
0.1 µg
5 TU
N/A | Day 6 to 8: Reading
Day 25 to 31: Reading for positive reactors                                                                                        |

\* Adverse Event assessment occurs at each reading time point.

Upon completion of Stage B, the SMC will review the data and a report will be sent to DMID, NHRC, and CSU IRB. Stage C will proceed upon approval from each of these authorities. Size and frequency of reactions will be a consideration in determining the use of one or both antigens as well as antigen dosages, in Stage C-1.

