Stage C-1b is a continuation of Stage C-1 to assess the reactivity of the low dose of each investigative antigen. There are indications from the blinded results arising from Stage C-1 that at least some individuals within the TB group react to more than one antigen (presumably the PPD and one of the leprosy antigens). Thus the inference is that the antigen concentration in some of the leprosy antigens is sufficiently high as to be cross reactive for TB and leprosy patients. For that reason Stage C-1b was designed to test the reactivity of the leprosy skin test antigens as the lower dose across the spectrum of patients. A small sample of 20 individuals from each group of the target populations (healthy contacts of BL/LL leprosy patients, BL/LL leprosy patients, BT/TT leprosy patients, and TB patients) will receive the low dose (0.1µg) of each test antigen, and a 2TU dose of tuberculin/PPD. Data will be reviewed by the SMC, and a report will be sent to DMID, NHRC, and CSU IRB.

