## 4.7 Interim Analysis Plans

Upon the completion of each stage, The EMMES Corporation will analyze and compile data into a safety report to be reviewed by the SMC. Data from Stage A will be reported “blinded,” since Stage A is merely a ramping stage for Stage B. Following Stage B, both Stage A and B will be unblinded and analyzed together. Upon review of Stages A/B, C-1 and C-1b, the SMC will compose a report to be sent to DMID, NHRC, and CSU IRB. In all cases of unblinding, the identity of antigens will only be made available to key study personnel.

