## 17 DATA HANDLING AND RECORD KEEPING

### 17.1 Data Management Responsibilities

Data collection is the responsibility of the clinical trial staff at AH under the immediate supervision of the SC, and overall supervision of the Principal Investigator. During the study, the Principal Investigator will maintain complete and accurate documentation for the study. All source documents and laboratory reports will be reviewed by the clinical team and data entry staff, who will ensure that they are accurate and complete. AEs must be graded at the time of occurrence, assessed for severity and causality, and reviewed by the site Principal Investigator or designee. SAE reports will be generated by the SC and reviewed by the PI, prior to sending to PPD Development Inc., DMID's pharmacovigilance contractor, DMID Medical Monitor and the DMID PO.

Data collected at the clinical site will be checked at the DCC for anomalies and inconsistencies through the DCC's Data Integrity Evaluation System, as described in Section 14, "Access to Source Data/Documents". The DCC will be responsible for ensuring accuracy of data, analyzing the data, and preparing safety and sensitivity/specificity reports following each study stage. Additionally, data will be collected from the two laboratory assays. A compilation of this data will be sent to the DCC for inclusion in the sensitivity/specificity report for Stage C. Various reports are required throughout the study: (1) If an SAE occurs, the SC is responsible for generating a report from the SAE Form, to submit to the DMID PO, ORA, SMC and the DCC; (2) The DCC is responsible for generating a safety report following each study stage, for submission to the DMID PO and the SMC; (3) The SMC Chair is responsible for generating an SMC report summarizing the SMC recommendations following an *ad hoc* meeting to review an SAE, or following a study stage review; and, (4) The study PI is responsible for generating a final study report to submit to the DMID PO and ORA. The study sponsor will keep each report. Following the completion of the study, all data source documents, analysis files and reports will be transferred to the DMID PO for retention.

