### 17.4 Timing/Reports

Reviews and reports are periodic. Upon completion of each sequential stage, the DCC will analyze the data and compile a safety and/or sensitivity/specificity report, depending on the stage of the study under evaluation. This report will be submitted to the SMC for review. Following appraisal of the data by the SMC, the SMC Chair will summarize the committee's recommendations in a report to be submitted to DMID, NHRC and CSU IRB. Subject to approval from each of these authorities, the study will proceed to the next stage (no earlier than 4 days after the final reading of the previous stage), until the end of Stage C-1b. At this time, a final report will be submitted by the study PI to the study sponsor and both HRCs.

Safety and sensitivity/specificity outcome measures described in Section 17.3, "Types of Data", will be used to evaluate each study stage. In addition, data such as BCG scar size, age and gender, which is collected during the enrollment process, may also be used to evaluate study antigens. Tables reported by the DCC for appraisal of safety and sensitivity/specificity will include, but not be limited to: listing demographic characteristics; Listing of readers' assessments of erythema and measurement of induration; summary of skin test readings by antigen code (induration and erythema); summary of 15-minute reaction record and 30 minute reaction record (for State C1b only); summary of follow-up examination and reaction form; and listing of all AEs (including observations noted between 15-30 minutes after antigen administration for stage C1b) and SAEs. The safety report summarizing Stages A and B will be reviewed by the SMC to determine if skin test antigens, MLSA-LAM and MLCwA at the administered dosages, are safe to use in human subjects. Likewise, the safety report summarizing data from Stage C-1 will be reviewed before Stage C-1b begins. Subsequently, following Stage C-1b, the safety report will be analyzed according to plans outlined in Section 13.9, "Analysis Plan".

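### Section 13.8 calls every interim look a safety look, but C-1b was added on reactivity seen in C-1, so the C-1 versus C-1b dose test is confounded with stage and tilted towards the low dose

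*Protocol*

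**What the plan says.** Section 13.8 opens with "Interim analyses planned for this study are all directed at monitoring safety and the overall conduct of the trial" and continues with "These analyses should not impact the Type I error, or equivalently the length of confidence intervals, for the primary computations of sensitivity and specificity". Later in the same section, the interim tables are to include induration readings by subject and antigen code. Induration is the primary outcome measure (13.4) and the basis of the ROC, sensitivity and specificity work (13.9.3).

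Other sections give reactivity a role in the design:

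- Protocol Summary, Stage B, on the choice for C-1: "Size and frequency of reactions will be a consideration in determining the use of one or both antigens as well as antigen dosages". Section 4.7 adds "Following Stage B, both Stage A and B will be unblinded and analyzed together".
- Protocol Summary, Stage C-1b: the stage rests on "indications from the blinded results arising from Stage C-1 that at least some individuals within the TB group react to more than one antigen", and the text gives this as the reason for testing the lower dose.
- Section 17.1 makes the data centre responsible for "preparing safety and sensitivity/specificity reports following each study stage". Section 17.4 has it "compile a safety and/or sensitivity/specificity report, depending on the stage of the study under evaluation". Section 10.1 instead places the sensitivity/specificity assessment at the end of Stage C.

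Section 13.2 names TB patients, with healthy unexposed subjects, as the negative control group. Section 13.6.2 keeps C-1 (1.0 µg) and C-1b (0.1 µg) apart for ROC, sensitivity and specificity. Section 13.9.3 then plans to compare antigens and doses for a statistically significant difference in area under the curve.

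**The concern.** Cross-reaction in TB patients is a specificity result. Adding 80 of the 160 Stage C subjects because of it means that an outcome-type finding shaped the design, which 13.8 says did not happen.

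Blinding does not remove the difficulty. Each C-1 subject has three sites (two leprosy antigens and PPD, no saline), and the disease group is known. A TB patient who reacts at two sites has therefore reacted to at least one leprosy antigen. The Stage C-1b text draws much the same inference.

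What is at stake is the dose comparison. No subject in Stage C is randomised between doses, the stages run one after the other, and the comparison exists only because the first stage showed cross-reaction. Section 2.2 ties future studies to sensitivity and specificity of about 90% or above, so a shift of several points in apparent specificity could be over-read as a merit of the lower dose.

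**Working it through.** Section 13.8 gives no figure to reproduce. The check has two parts.

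**1. Intervals within a dose.** C-1b excludes earlier participants (5.3) and is not pooled with C-1 (13.6.2), so its sample is untouched by the C-1 result and its intervals keep nominal coverage. C-1 was completed and not stopped on its own results (13.7), so its intervals keep nominal coverage unconditionally. On this point the sentence in 13.8 stands, though not for the reason it gives.

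**2. Comparison between doses.** Suppose both doses have the same true TB reaction rate p, and C-1b is added only if at least k of n TB patients react in C-1.

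Inputs:
- n = 20 per group, or 18 after the 10% loss used in 13.6.1.
- p and k are assumptions. The protocol says only that some individuals reacted.

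Formula: tilt = E[X | X ≥ k]/n − p, with X binomial(n, p). C-1b is unselected, so its expected rate is p.

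The trigger probabilities agree with the n = 18 binomial table in 13.6.1. At p = 10%, P(X ≥ 1) = 1 − 0.9^18 = 84.99% and P(X ≥ 3) = 26.62%.

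- k = 1, n = 18, p = 10%: 0.10/0.8499 − 0.10 = 1.8 points. With n = 20: 0.10/0.8784 − 0.10 = 1.4 points.
- k = 3, n = 20, p = 10%: P(0), P(1), P(2) = 0.1216, 0.2702, 0.2852, so P(X ≥ 3) = 0.323. The conditional mean is (2 − 0.2702 − 2 × 0.2852)/0.323 = 3.59, or 17.9% of 20. Expected TB specificity is 82% in C-1 against 90% in C-1b, a tilt of 7.9 points.
- k = 3, n = 18, p = 10%: (1.8 − 0.3002 − 2 × 0.2835)/0.2662 = 3.50, or 19.5% of 18. The tilt is 9.5 points.

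Over a range of true rates, n = 18. The second figure is the chance that a two-sided 5% pooled z test of the two TB reaction proportions falsely favours the low dose (nominal 2.5%):

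| Trigger | p = 5% | p = 10% | p = 20% | p = 30% |
|---|---|---|---|---|
| ≥1 | 3.3 points; 0.7% | 1.8; 2.0% | 0.4; 2.4% | 0.0; 2.5% |
| ≥2 | 7.8; 1.9% | 5.2; 3.0% | 1.7; 2.6% | 0.4; 2.5% |
| ≥3 | 12.9; 7.5% | 9.5; 6.3% | 4.2; 3.3% | 1.3; 2.7% |

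Three limits apply.
- The proportion test stands in for the planned AUC test.
- The trigger is counted on the antigen being compared. Under blinding it was a reaction to either leprosy antigen, so the tilt for one antigen is smaller unless the two react together.
- The tilt enters through TB patients only. If BL/LL patients, unaffected by the trigger, are pooled with an equal number of TB patients as negatives, it halves: 3.3/2 = 1.7 points at most for a trigger of one, and 7.9/2 to 9.5/2 = 4.0 to 4.8 points for three at p = 10%. With BL/LL patients alone this route is absent. The confounding with stage remains in every case.

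**The case against.** The strongest defence is that the protocol is descriptive. Section 13.5 disclaims formal hypotheses, 13.6.2 says that its power figures do not set a criterion for success, and multiplicity is openly left to the data analysis. Both doses were under evaluation from the start, and both antigens at both doses reached Stage C, so the Stage B option removed nothing in the design shown. C-1b also has a safety objective (13.1.2). It came by amendment from blinded results, whereas 13.8 describes planned looks.

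Much of this stands, and it rules out stronger readings. A reader might infer that the interim look gives each antigen a second 5% test and raises its error to 1 − 0.95² = 9.75%, or further over both antigens. The documents do not support that. The second test comes from analysing two doses separately and would exist with no interim look, the protocol makes no claim that either dose suffices, and 13.6.2 already defers the multiplicity. For the same reason, wider intervals such as 97.5% are not called for, and they would not remove the tilt.

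A reader might also infer that sensitivity was computed after every stage. Stages A and B contain no leprosy patients, 17.4 says the content depends on the stage, and 17.4 describes the report reviewed before C-1b as a safety report. The wording of 17.1 is loose, but it is not proof of an interim accuracy analysis.

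The defence does not reach two points. The stated purpose of the looks in 13.8 is incorrect, and 13.9.3 still plans a significance test across stages.

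**Conclusion.** The point holds in a limited form. Section 13.8 misdescribes the role of interim data, because reactivity informed antigen and dose use and prompted C-1b. Sensitivity and specificity intervals within each dose are not harmed. The C-1 versus C-1b test is confounded with stage and, if the doses are truly identical, tilted towards the low dose.

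The direction is clear but the size is not. TB specificity shifts by about 0-3 points with a trigger of one or more reactors, where false favouring stays at or below the nominal 2.5%. It shifts by about 8-10 points with a trigger of three or more at a 10% true rate. These figures rest on an assumed trigger and assumed rates, and on the trigger being counted on the antigen compared. The comparison of the two antigens within a stage is not affected by the confounding, since each Stage C subject receives both.

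**What to change.** - **13.8:** replace the opening statement. Say that reactivity data from Stages A/B and C-1 informed antigen and dose use and the addition of C-1b. Say that intervals within each dose keep nominal coverage because C-1b subjects are new and not pooled with C-1.
- **13.9.3:** state that the C-1 versus C-1b comparison is exploratory, non-randomised and confounded with stage. Report it as an estimate with its interval, and make no claim of a significant dose difference.
- **17.1 and 17.4:** align with 10.1, so that sensitivity/specificity is assessed and reported at the end of Stage C.

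The cost is wording in four sections, with no new data. What is given up is a significance claim for dose, which this design cannot support. Section 13.7 says that C-1 was complete before the amendment and C-1b was still ahead, so the change can be made before C-1b data exist.
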